#### Ethical and legal issues

The Ethics and Research Committee of Malaga (Northwest District) granted the approval for this trial. The regulations on Good Clinical Practice will be observed at all times, as well as the ethical principles established for the research on human beings stipulated in the Declaration of Helsinki and further amendments thereto. The clinical information will remain separate from the identification details and the databases will be coded and stored in specific computers solely intended for the project. All the records will be made observing all the dispositions from the legislation in force with regard to personal data protection according to the Act 15/1999 dated 13 December, as well as on safety of computerized files which may store personal data information, and more specifically, with regard to the access through communication networks (Royal Decree 994/1999 dated 11 June) and access to confidential information for scientific purposes from the Commission Regulation CE No. 831/2002 by the European Union and Act 41/2002 dated 14 November, which is considered the legal standard on Patient’s Autonomy and Rights and Duties in terms of Clinical Information and Documentation.

The staff responsible for such purpose will manage the data according to the instructions provided by the person responsible for the treatment. Such data will not be applied or used for a different purpose than those stated in the respective authorization; neither will they be reproduced to other people even for registration purposes. Once the aim of the trial has been carried out, the personal data collected will be destroyed, deleted, or given back to the person responsible for the treatment, along with any other media or documents containing any personal data related to the project. Every patient will be informed verbally and in writing about the objectives of the project and its methodology. Each individual will sign the respective informed consent form.

## Discussion

Pressure ulcers are nowadays considered an important health issue causing a great economic impact by substantially increasing pharmaceutical expenditure. The total expenditure of pressure ulcer treatments amounts to 5% of annual health care expenditure and causes a higher health care burden on professional staff. This is a public health problem, which affects mainly older people, thus, this disease rate is increasing.

The acceptance of our hypothesis will provide evidence supporting the regular use of olive oil (nonoxygenated fatty acids) in the prevention of pressure ulcers in primary health care, likewise involving hospital care. Furthermore, owing to the lower price of the product, primary health care districts may consider purchasing them, owing to the reduction in health care workload for professional staff, as well as for the family caregivers, given that the incidence of pressure ulcers will be lower as well as the respective reduction in pharmaceutical expenditure.

The main limitation of the trial is that when performing the cost-effectiveness analysis, the variables on caregiver inputs may not be estimated, along with those variables regarding the expenditure derived from the patient’s suffering. Likewise, there might be a selection bias due to those patients who refuse to take part in the trial, which may involve differential baseline characteristics. For the purposes of this trial, in the analysis it will be taken into account whether there are differences among those who take part in the trial and those who do not. The same procedure will be applied for withdrawals during the follow-up period. The analysis will be carried out according to the protocol and intention to treat. In the event that the results of the two types of analysis do not match, the subgroup of patients who did not comply with the protocol will be studied, to determine the reasons before reaching a final conclusion of noninferiority.

The confusion bias derived from some variables such as age, sex, type of intervention, and nutritional status of the patient will be managed during the statistical analysis stage, by means of a multivariate analysis.

The usual application of olive-oil-based formulas may be helpful in preventing the appearance of any grade of pressure ulcer in immobilized patients, and thus, it will be a cheaper treatment and may be considered as an alternative treatment.

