The main role of the oil is its antioxidant function: for this purpose, the oil should have a low peroxide content and a high polyphenol content. Extra virgin olive oil includes 330 to 500 mg of polyphenols per kg of fat and less than 20 milliequivalent (mEq) weight of peroxide per kg of fat (the composition of the HOFAs includes from 40 to 50 mg of polyphenols per kg of fat and from 230 to 340 mEq of peroxide per kg of fat). Owing to its lipid composition, it is completely compatible with of human tissue cells, which means that its topical use does not cause allergy or irritation. Such properties lead us to consider a possible protective effect on the appearance of pressure ulcers, similar to those of HOFA, but at a much cheaper cost, as well as offering an alternative treatment option. Furthermore, there are no previous experiments with this product in the prevention of pressure ulcers in nursing care at home. The main aim of this trial is to assess whether the effectiveness of olive oil use is lower or higher than the HOFA in the prevention of pressure ulcers in immobilized patients receiving nursing care at home and, as a secondary aim, to assess the cost-effectiveness of this new intervention with regard to the use of HOFA.

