## Methods/design

The design of this study is a noninferiority, triple-blinded, parallel, multi-center, randomized clinical trial. The blinded groups are the patients and their caregivers, nurses and the research group.

The null hypothesis of this study is that the difference in the appearance of pressure ulcers in immobilized patients at home who receive olive oil (*G*_o_), in contrast to those patients applying HOFA (*G*_h_) is higher than the delta value established at 10% (*H*_0_ = *G*_o_ − *G*_h_ > 10%), that is to say, that the lower bound of the confidence intervals includes that 10%. In the event that it is possible to reject the null hypothesis, the alternative hypothesis of this study will be that olive oil is not lower than 10%, compared with the HOFA (*H*_1_ = *G*_o_ − *G*_h_ < 10%); in other words, the lower bound of the confidence interval of the difference between both products is lower than 10%.

Two procedures will be performed: usual care and application of HOFA to the control group and usual care and application of an olive-oil composition to the target group. The main outcome will be the appearance of grade 2 pressure ulcers. The accuracy of the trial with regard to the control medicine (HOFA) is widely supported, owing to the favorable historical results of such medicine against placebo [25] as per recommendations of the International Conference of Harmonization and also because the efficiency conditions of the mentioned medicine will be met for the purpose of this trial.

The target population will be patients included in the immobilized-patients program within the nursing care at home service provided in Health Centers in Andalucía (Spain), and more specifically in the regions of Malaga, Granada, Seville, and Cadiz.

The inclusion criteria will be: patients over 18 years; not having pressure ulcers; patients supported by a family or a remunerated caregiver for the application of the treatment; diagnosed by a nurse as a ‘risk for impaired skin integrity’, by applying the Braden Scale for prediction of pressure ulcer risk, showing a high risk (score ≤ 12) or moderated risk (score 13 to 16), and; patients with nutritional status assessed according to the Mini Nutritional Assessment scale scoring 10 or less.

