As exclusion criteria, the following were established: the patient declines to take part in the trial; patients with a usual address different from the area of the health center where the study is carried out, or plans to be away from the usual address during the follow-up period; those patients who have been hospitalized during the sampling period; terminally ill patients or those who already have pressure ulcers.

All the patients included in the trial will receive the information concerning the aim of the trial in writing, which will be duly signed by the researchers. The patients will confirm their participation in the trial and sign an informed consent form. In those cases when the patients have cognitive impairment, the legal guardian will be the one who signs the informed consent form. Patients who do not confirm their consent will be substituted by other patients selected by the same procedure of general randomized selection, thus, extending the selection process as long as necessary.

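### The Discussion treats lower ulcer incidence as a consequence of accepting a noninferiority hypothesis, which can be accepted with olive oil observed 2 to 3 points worse than HOFA

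*Protocol article*

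**What the plan says.** Methods/design in the protocol article fixes the design: "The design of this study is a noninferiority, triple-blinded, parallel, multi-center, randomized clinical trial". The alternative hypothesis is that ulcer incidence on olive oil minus incidence on HOFA is below 10 points, worded as "the alternative hypothesis of this study will be that olive oil is not lower than 10%, compared with the HOFA". Sample selection sizes the trial for that hypothesis alone, with 45% incidence assumed in both arms. Statistical analysis decides the main question by setting the confidence interval of the difference against delta.

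The Discussion opens its conclusions with "The acceptance of our hypothesis will provide evidence supporting the regular use of olive oil". Its next sentence says that health districts may consider buying the product because workload will fall, "given that the incidence of pressure ulcers will be lower as well as the respective reduction in pharmaceutical expenditure". The sentence before that also widens the setting: "in the prevention of pressure ulcers in primary health care, likewise involving hospital care". The population is home-care patients only, and the exclusions include "those patients who have been hospitalized during the sampling period".

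The main aim, at the end of the Background, is put differently again: "to assess whether the effectiveness of olive oil use is lower or higher than the HOFA".

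**The concern.** The Discussion makes lower incidence follow from acceptance of the hypothesis. That hypothesis allows an excess of ulcers on olive oil of anything under 10 points, so acceptance cannot carry the claim. The claim is aimed at purchasing by health districts, so a result that means not more than 10 points worse could be read as fewer ulcers and less nursing work.

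The aim adds a smaller mismatch. It asks a two-directional question about effectiveness, while the hypothesis is one-directional with a 10-point allowance. Aim, hypothesis and conclusion are therefore three different statements, and nothing in the article says which result would justify saying that incidence is lower.

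**Working it through.** **Inputs.** From Sample selection: incidence 45% in both arms, margin 10 points, one-sided 5%, power 80%, 306 per arm before withdrawals, 15% withdrawal. From Statistical analysis: 95% confidence intervals. The difference d is olive oil minus HOFA, so an excess of ulcers is positive and noninferiority requires the upper limit of d to be below 0.10.

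**The plan's own figure.** n per arm = (1.645 + 0.842)² × 2 × 0.45 × 0.55 / 0.10² ≈ 306.0 (307 if rounded up), against the stated 306. With withdrawal, 306 / 0.85 = 360 per arm, as stated. The sample size reproduces, and it assumes no benefit of olive oil over HOFA.

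**Largest observed excess that still passes.** SE = √(2 × 0.45 × 0.55 / 306) = 0.0402.
- Two-sided 95% limit: 0.10 − 1.960 × 0.0402 = 0.021.
- One-sided 5% limit: 0.10 − 1.645 × 0.0402 = 0.034.

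In whole patients, with unpooled limits and HOFA at 138/306 (45.1%):

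| Limit used | Olive oil | Observed d | Upper limit of d |
|---|---|---|---|
| Two-sided 95% | 144/306 (47.1%) | +2.0 points | +9.9 points |
| One-sided 5% | 148/306 (48.4%) | +3.3 points | +9.9 points |

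Both results meet the margin. With all 360 per arm analysed and HOFA at 162/360, the passing excess grows slightly, to 2.5 and 3.6 points.

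**How often this would happen if the true rates are equal at 45%.** The chance of success is Φ(0.10/SE − z), and half of all trials would show d above 0.
- Two-sided 95% limit: success 0.701; success with d above 0 is 0.701 − 0.500 = 0.201; share 0.201 / 0.701 = 29%.
- One-sided 5% limit: success 0.800; success with d above 0 is 0.300; share 0.300 / 0.800 = 37%.

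**Power of a later superiority test** (two-sided 5%, 306 per arm, unpooled normal approximation). The reductions are assumptions for illustration; the article gives none.
- 45% against 40%: SE = √((0.2475 + 0.2400)/306) = 0.0399; Φ(0.05/0.0399 − 1.96) = 24%.
- 45% against 35%: SE = √((0.2475 + 0.2275)/306) = 0.0394; Φ(0.10/0.0394 − 1.96) = 72%.

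**The case against.** The other side has several fair points.

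- The clause is motivational text in a Discussion. No decision rule or sample size depends on it. The same section later speaks of a conclusion of noninferiority and hedges most of its recommendations. This stands, and it limits the point to interpretation.
- A reader might infer that the main aim also claims lower incidence. It does not: it asks whether effectiveness is lower or higher, and lower effectiveness would mean more ulcers. The aim only fails to match a one-sided hypothesis.
- A reader might infer that noninferiority is the only test planned, so that superiority could never be shown. The article does not support that. Statistical analysis also plans absolute and relative effect measures with 95% intervals, chi-squared tests, and Kaplan-Meier curves with a log-rank test. An interval wholly below 0 would be evidence of lower incidence. What remains is that none of these is designated to support that claim. A formal step might stand in an analysis plan that is not shown, so its absence is not the fault. The fault is that the Discussion ties lower incidence to acceptance of the stated hypothesis.
- The comparator of the lower incidence is not named. It could be no product at all, resting on HOFA's earlier results against placebo. The trial has no such arm, so its own data would not show this reading either.
- Workload is measured, since nurse visits enter the cost analysis. This stands, but the Discussion derives the workload saving from lower incidence, not from that comparison.
- Passing with a slightly worse point estimate is possible in any trial with a positive margin. That is true, and the figures show no error in the sizing. They show why success cannot be reported as a reduction.

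**Conclusion.** The point holds as a modest one about what the trial may conclude. Acceptance of the stated hypothesis supports only that olive oil is not more than 10 points worse than HOFA, in the home-care patients enrolled. The lower incidence, and the workload saving derived from it, do not follow. The mention of hospital care likewise goes beyond the population studied.

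The size is an observed excess of about 2 points (two-sided 95% limit) to 3 points (one-sided 5% limit) compatible with success, and 29% to 37% of successes with olive oil numerically worse. These figures assume 306 evaluable patients per arm, a HOFA incidence of 45% and a normal approximation; the shares also assume equal true rates.

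It would go too far to say that the plan is committed to a claim of superiority, or that its analysis is invalid. Its decision rules concern delta only.

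**What to change.** 1. In the Discussion, replace the lower-incidence consequence with a conclusion that olive oil is not more than 10 percentage points worse than HOFA in home-care patients, and drop the extension to hospital care.
2. Reword the main aim in the Background as a noninferiority question with the 10-point margin.
3. By a documented amendment before unblinding, state the order of claims. First comes noninferiority: upper limit of olive oil minus HOFA below 10 points in the planned per-protocol analysis, with a consistent intention-to-treat result. Only then may lower incidence be claimed, and only if the upper limit of the two-sided 95% interval in the intention-to-treat set is below 0. The two steps use different analysis sets, so the text should name the set for each.

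The fixed order needs no alpha adjustment and no extra patients. The cost is a short amendment during enrolment, and a superiority step with low power for small effects: about 24% for an assumed 5-point reduction and 72% for an assumed 10-point reduction.

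The amendment should also say which limit decides noninferiority. If it is the two-sided 95% limit, as Statistical analysis implies, power at 306 per arm is about 70% and not the stated 80%, and this should be disclosed. That loss comes from the existing text, not from the added step.

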### Sample selection

The directors and care service coordinators of each health center will be duly informed about the trial, and they will be asked for their availability as well as their consent to take part in the trial. Nursing staff of each health center who so desire will be able to take part, being in such case responsible for the research study implementation and follow-up in their respective health center.

Records of patients included in the nursing at home program for immobilized patients will be assessed to determine whether patients comply with the inclusion requirements. At this point, such patients will sign the informed consent form and subsequently, their details will be randomized by a computer system independent of the professional staff, which will be processed at the clinical trial control center.

To achieve a power rate of 80.00% to reject the null hypothesis (*H*_0_: the difference between proportions *p*1 and *p*2 is lower than the noninferiority bound), using a normal asymptotic analysis test (noninferiority), unilateral proportions for two independent samples, taking into account that the level of statistical significance is 5.00%, and assuming that the proportion in the reference (control) group is 45.00% and the proportion in the experimental group is 45.00% [9], the proportion of experimental units in the reference group is 50% related to the total and the noninferiority bound (delta) is 10.00%, then, it will be necessary to include 306 experimental units in the reference group and 306 units in the experimental group, totalling 612 units in the study. Taking into account that the expected withdrawal rate is 15.00%, it will be necessary to enroll 360 experimental units in the reference group and 360 units in the experimental group, totalling 720 experimental units in the trial.

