For the analysis on cost-effectiveness, the effectiveness measures previously established (*U*_1_ and *U*_0_) will be obtained. The increase in cost for each option (Δ*C*_*ij*_) will be estimated, as well as the increase of effectiveness rate, when comparing the two options, the cost-efficiency ratio of each treatment and the incremental cost-effectiveness ratio of each option. These values will enable us to assess the necessary cost to increase by 1% the possibilities of success when preventing pressure ulcers in these patients by using each product.

The analysis will be carried out according to the protocol, as established for the noninferiority studies, to ensure the difference conditions between the treatments and increase the rejection conditions of the null hypothesis. Nevertheless, an analysis will be carried out that is intended to compare both analyses and assess, if the analyses differ, the subgroups of patients who did not comply with the trial protocol with the aim of identifying the possible reasons for the withdrawal from the trial, before accepting or rejecting the null hypothesis. The confidence intervals of the main result variable will be analyzed to determine whether the difference found is within the bound established for the delta value. Statistical analysis will be performed using SSPS 20 software.

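### If the per-protocol and intention-to-treat results disagree, no rule says which prevails, so noninferiority is decided at discretion after both results are known

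*Protocol article*

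**What the plan says.** Protocol article, Statistical analysis: "The analysis will be carried out according to the protocol, as established for the noninferiority studies". One reason given is to "increase the rejection conditions of the null hypothesis". The section then compares both analyses. If they differ, it provides for assessing "the subgroups of patients who did not comply with the trial protocol with the aim of identifying the possible reasons for the withdrawal", and places this step "before accepting or rejecting the null hypothesis".

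Protocol article, Discussion: "The analysis will be carried out according to the protocol and intention to treat", in no stated order. On a mismatch, "the subgroup of patients who did not comply with the protocol will be studied, to determine the reasons before reaching a final conclusion of noninferiority".

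Intention to treat is named as the second analysis only in the Discussion. The leading place of the per-protocol analysis rests on the Statistical analysis section.

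**The concern.** The look at non-compliers is triggered by the mismatch itself, so both results are known by the time it happens, and the decision on the null hypothesis comes after it. No criterion links what is found to what is concluded. One team could set aside an unfavourable per-protocol result because the exclusions looked odd. Another could set aside an unfavourable intention-to-treat result because the non-compliers explain it. Both would be following the text.

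The stake is the primary claim. A noninferiority test has its stated error rate only if the event that counts as success is fixed in advance. Here that event is undefined whenever the two sets disagree. Blinding of the research group, stated in Methods/design, reduces some bias but does not supply the missing criterion.

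**Working it through.** **Inputs from Sample selection.** Ulcer rates 45% and 45%, margin 10 points, one-sided 5%, power 80%, 1:1 allocation, 306 evaluable per arm, 15% withdrawal, 360 enrolled per arm. The Statistical analysis section uses 95% intervals. Reading one limit of such an interval is a one-sided 2.5% test, so both levels are shown.

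**The plan's own figure.** n per arm = (1.6449 + 0.8416)² × 2 × 0.45 × 0.55 / 0.10² = 306.04, against 306 stated. Then 306 / 0.85 = 360, as stated. The sample size is not in question.

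**Assumptions, not in the documents.** The intention-to-treat set has outcomes for all 360 per arm. The per-protocol set is 306 per arm, with 15% excluded in each arm. Exclusion is unrelated to outcome. The correlation between the two test statistics is then about √(306/360) = √0.85 = 0.92.

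**Power of each set alone, by formula.** Power = Φ(0.10 / √(2 × 0.45 × 0.55 / n) − z).
- n = 306, one-sided 5%: Φ(2.486 − 1.645) = 80.0%. With the 95% interval: Φ(2.486 − 1.960) = 70.1%.
- n = 360, one-sided 5%: Φ(2.697 − 1.645) = 85.4%. With the 95% interval: Φ(2.697 − 1.960) = 76.9%.

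**Simulation.** There were 400,000 trials per scenario. Noninferiority was declared when the unpooled upper confidence limit for olive oil minus HOFA was below 10 points.

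| Scenario | Level | Per protocol | Intention to treat | Either | Both | Disagree |
|---|---|---|---|---|---|---|
| Equal, 45% v 45% | 5% | 80.2% | 85.8% | 87.6% | 78.5% | 9.1% |
| Equal, 45% v 45% | 2.5% | 70.2% | 76.4% | 79.1% | 67.5% | 11.6% |
| At the margin, 55% v 45% | 5% | 5.2% | 4.7% | 6.6% | 3.4% | 3.2% |
| At the margin, 55% v 45% | 2.5% | 2.5% | 2.4% | 3.4% | 1.6% | 1.8% |

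**Reading the table.**
- With truly equal products, about one trial in eleven reaches the undefined branch at one-sided 5%, and about one in nine with the 95% interval. At 5%, most of these pass by intention to treat only (87.6 − 80.2 = 7.4 points). The rest pass per protocol only (87.6 − 85.8 = 1.8 points).
- At the margin, letting either set carry the claim gives about 6.6% instead of 5%, or 3.4% instead of 2.5%. Requiring both gives 3.4% or 1.6%.

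**Why the fix names both sets.** Two further assumed scenarios, both at one-sided 5%:
- The overall difference is exactly 10 points, but the 15% excluded from the olive-oil arm have a 75% ulcer rate. Per protocol alone then passes in about 22% of trials, and requiring both passes in about 4.4%.
- Compliers differ by 10 points and non-compliers not at all. Intention to treat alone then passes in about 10%, and requiring both in about 4.6%.

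These only illustrate that neither set is safe alone. They are not estimates for this trial.

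**The case against.** **Per protocol is a recognised lead analysis for noninferiority.** This stands. Choosing it is not an error, and running both analyses is good practice. The plan also compares withdrawals with other participants (Discussion), which partly addresses selection.

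**The mismatch step may be a safeguard.** If studying the non-compliers could only withhold a per-protocol claim, the error rate would stay at or below nominal when exclusions are unrelated to outcome. That is fair, but the text does not limit the step in that way. A reader might also infer the opposite, that either set suffices. The documents do not say that either, so 6.6% and 3.4% are outer bounds and not the plan's error rate.

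**The stated reason for per protocol may not be backwards.** A reader might infer from "increase the rejection conditions of the null hypothesis" that per protocol was chosen to make noninferiority easier to claim. The phrase can equally mean making the conditions for rejection stricter, which is the usual argument. The same sentence also speaks of ensuring the difference between treatments, which fits that reading. The wording is unclear, but a reversed rationale is not shown.

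**An unseen analysis plan may settle it.** It may add a rule. But the article states the post hoc step twice as the route to the conclusion, so a fixed rule would have to replace this text and not merely add to it.

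**The issue is often moot.** When the two sets agree, which is about nine trials in ten under equal products, nothing turns on it. This stands and limits the weight of the point.

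**Conclusion.** The concern holds in a limited form. The plan fixes its rule for disagreement badly: the noninferiority decision is left open until both results are known, with no criterion. Under equal 45% rates this branch is reached in about 9% of trials at one-sided 5%, and in about 11–12% with the 95% interval. The worst-case type I error is about 6.6% or 3.4%. All of this assumes 15% exclusion per arm unrelated to outcome and complete intention-to-treat outcomes.

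Two further inferences should not be drawn. A wider error range would need a lower correlation between the two analyses than 15% exclusion implies. A figure for dilution would need withdrawn patients to be counted as ulcer-free in the intention-to-treat set, and the article does not say that they are. The change is worth making because it concerns the primary conclusion and costs little.

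**What to change.** Replace the mismatch rule in Statistical analysis and in Discussion with: *Noninferiority is concluded only if the upper confidence limit for olive oil minus HOFA is below 10 points in both the intention-to-treat and the per-protocol sets; if they disagree, noninferiority is not concluded.*

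Make three consequential edits:
- In Methods/design, the decision is worded through the lower bound of the interval. Align it with the upper limit, which is the one that matters for olive oil minus HOFA.
- Keep the study of non-compliers, but state that it is explanatory and cannot change the conclusion.
- Reword the phrase about rejection conditions so that the reason for the per-protocol analysis is unambiguous.

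The primary outcome and its estimator need not change. Trial status says enrolment and follow-up are under way, so the rule can be fixed before unblinding.

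**Cost.** At one-sided 5%, power is about 78.5% against 80.0% for per protocol alone by formula, a loss of about 1.5 points (1.8 against the simulated 80.2%). With the 95% interval it is about 67.5% against 70.1%, a loss of about 2.5 points. The planned 720 need not change for this reason.
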